#### Analysis of secondary endpoints

##### Efficacy - Antibody response

Participants will be classified as responders or non-responders [17]. Number and proportion of responders and non-responders at day 28 will be reported for each patient population. Pearson chi-2 test will be performed to assess whether antibody response differ between patient groups. In subsequent sensitivity analyses we will perform multiple regression analyses correcting for possible differences in age and sex between the patient groups. Additionally, in kidney transplant recipients we will investigate whether time after transplantation, and the different immunosuppressive regimens are associated with response rate.

To assess durability of response within each patient group, we will report and compare response at day 28 with response at month 6 after vaccination. Comparison will be made using McNemar test.

The association between antibody response after SARS-CoV-2 vaccination and protection against COVID-19 will be examined for each patient group separately. For this, we will compare the antibody response at 28 days after vaccination in patients who develop COVID-19 with the antibody response in patients who did not develop COVID-19. Similar comparison will be made at 6 months after vaccination. We will examine this by use of the t-test or if more appropriate a non-parametric test. Subsequently, in a logistic regression model using Youden’s index, a cut-off in the antibody response at 28 days will be defined to serve as a correlate of protection against COVID-19.

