**Contribution of this study**
Assessment of incidence and course of COVID-19 after various types of SARS-CoV-2 vaccination during a two-year follow-up period in not only patients on dialysis or kidney transplant recipients, but also in patients with CKD stages G4-G5.Quantitative analysis of antibody response after SARS-CoV-2 vaccination and its relationship with incidence and course of COVID-19 in patients with CKD stages G4-G5, on dialysis or after kidney transplantation compared with a control group.Monitoring of (serious) adverse events and development of anti-HLA antibodies.

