Recently, efficacy and safety of different SARS-CoV-2 vaccine types have been demonstrated to be high in the general population [5–8]. So far, patients with CKD stages G4-G5 or on KRT were not or in low numbers included in these trials [9]. It is well known that vaccination efficacy against other viruses such as hepatitis B and influenza is considerably lower in patients with severely impaired kidney function, due to the immunosuppressive effect of uremic waste products [10]. A lesser antibody response after vaccination is to be expected in kidney transplant recipients due to the use of immunosuppressive agents. A recent Call to Action by the ERA-EDTA Council and ERACODA Working Group included the advice to perform dedicated vaccination studies to address this important knowledge gap regarding the efficacy of SARS-CoV-2 vaccination [11]. Recent studies have demonstrated the humoral response following SARS-CoV-2 vaccination in patients on KRT. One study showed a robust humoral response in the majority of haemodialysis patients after SARS-CoV-2 vaccination [12], but in a different study when compared to a control group, antibody titres were significantly lower [13]. Another study demonstrated a significantly reduced antibody response in 34 solid organ transplantation patients compared to health care workers [14]. Current data on SARS-CoV-2 vaccination efficacy in kidney patients report on surrogate endpoints, such as antibody titres. Clinical endpoints are currently lacking in the assessment of the efficacy of SARS-CoV-2 vaccination in kidney patients.

Therefore, we established the RECOVAC consortium (**RE**nal patients **CO**vid-19 **VAC**cination) in the Netherlands with active participation of the Dutch Kidney Patients Association (NVN). This consortium will perform the **L**ong-term **E**fficacy and **S**afety of **S**ARS-**CoV-2** vaccination (LESS CoV-2) study. In this study we aim to assess efficacy of SARS-CoV-2 vaccination in patients with CKD stages G4-G5 and on KRT in comparison to non-vaccinated control groups in a large-scale national registry study. We hypothesize that kidney patients obtain lesser protection from SARS-CoV-2 vaccination.

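### The only test named for the day-28 antibody comparison between patient groups uses responder status; a comparison of anti-RBD level should be added beside it

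*Protocol article*

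**What the plan says.** All of this is in the protocol article unless noted.

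- **Classification and summary** (Efficacy - Antibody response): "Participants will be classified as responders or non-responders", by a cited criterion whose value is not printed. The day-28 summary is stated as "Number and proportion of responders and non-responders at day 28 will be reported for each patient population".
- **Between-group test** (same section): "Pearson chi-2 test will be performed to assess whether antibody response differ between patient groups".
- **Adjusted analysis** (same section): "In subsequent sensitivity analyses we will perform multiple regression analyses correcting for possible differences in age and sex between the patient groups". The outcome scale is not given.
- **Transplant recipients** (same section): the question is whether time since transplantation and "the different immunosuppressive regimens are associated with response rate".
- **Graded use of the same measurement** (same section): within each patient group, antibody response is compared between those who do and do not develop COVID-19 by a t-test or a non-parametric test. A day-28 cut-off is then derived by Youden's index.
- **What is promised elsewhere**: the box on the contribution of the study announces "Quantitative analysis of antibody response after SARS-CoV-2 vaccination", together with its relation to COVID-19. The abstract (Methods) says the level of response will be assessed in subgroups. Table 3 lists the day-28 antibody response as a secondary endpoint without defining it as binary.
- **Numbers** (Study enrolment): antibody measurement is intended in 4000 CKD G4-G5, 4000 dialysis and 4000 transplant patients.

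**The concern.** The first secondary endpoint is measured on a graded scale, but the one test named for comparing the three patient groups keeps only whether each value passes a threshold. Information is lost in two ways. Where nearly everyone passes, a real shift in level moves the responder proportion very little. Where the groups have equal responder proportions but different levels among responders, the test has nothing to detect.

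The threshold is also not the one the study cares about most. It comes from a citation, whereas the protective cut-off is an output of this study. Two groups could be reported as having a similar antibody response although their levels differ, while the same article plans to use the level to predict protection. The same limit applies to the analysis of immunosuppressive regimen and time since transplantation.

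**Working it through.** **1. The plan's own figure.** The article states no alpha, power, response rate or titre SD for this comparison. The only figure to reproduce is the total: 3 × 4000 = 12,000, which agrees with the abstract.

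**2. Is a graded value available?** The Antibody measurement section speaks of the presence of antibodies, so this has to be inferred. A t-test and a Youden cut-off make no sense on a yes/no variable, and the abstract refers to level. A graded value must therefore be in the data.

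**3. Assumptions.** Log-titre is normal with equal SD (set to 1) in both groups. Comparisons are pairwise with n = 4000 per group at two-sided 5%, without multiplicity adjustment. Responder rates are illustrative.

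**4. Information kept by the cut.** With responder rate p and cut-point c = Φ⁻¹(p), the asymptotic efficiency relative to the full scale is φ(c)² / [p(1 − p)].

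- p = 50%: 0.3989² / 0.25 = 0.64
- p = 80%: 0.2800² / 0.16 = 0.49
- p = 90%: 0.1755² / 0.09 = 0.34
- p = 95%: 0.1031² / 0.0475 = 0.22
- p = 99%: 0.0267² / 0.0099 = 0.07

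At 95%, 4000 × 0.224 ≈ 900 per group: the responder analysis carries about the information of 900 per group analysed on titre.

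**5. Worked case, 95% v 94%.** The implied shift is 1.645 − 1.555 = 0.090 SD.

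- Chi-2: SE = √[(0.95×0.05 + 0.94×0.06)/4000] = √(0.1039/4000) = 0.00510. Then z = 0.01/0.00510 = 1.96, and power = Φ(1.96 − 1.96) ≈ 50%.
- Full-scale comparison of means: z = 0.0901 × √(4000/2) = 4.03, and power = Φ(4.03 − 1.96) ≈ 98%.
- Simulation (1000 replicates, titres below the cut-off set to the cut-off): chi-2 51%, Mann-Whitney 97%.

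**6. Other settings, 4000 per group.** Chi-2 power by normal approximation; Mann-Whitney power on floored titres by simulation where run.

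| Responders | Chi-2 | Mann-Whitney |
|---|---|---|
| 98% v 97% | 82% | about 100% |
| 97% v 96% | 68% | about 100% |
| 95% v 94% | 50% | 97% |
| 60% v 57% | 78% | 89% |
| 98% v 96% | 99.9% | – |
| 97% v 95% | 99.5% | – |
| 95% v 93% | 96.5% | about 100% |
| 90% v 87% | 98.8% | – |
| 80% v 76% | 99.1% | – |
| 60% v 55% | 99.5% | – |

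Material loss appears at 1-point differences near the ceiling. At rates of 87% to 98%, a 2- to 3-point difference already gives chi-2 about 97% to 100% power. In mid-range a slightly larger difference is needed: 3 points at 60% gives 78%, 5 points gives 99.5%.

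**7. Differences wholly above the cut-off.** Suppose both groups have 95% responders (0.95 × 4000 = 3800 each) and responders differ 1.25-fold in geometric mean titre, so log10(1.25) = 0.0969.

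- Assumed log10 SD 0.8: z = (0.0969/0.8) × √(3800/2) = 5.28, and power = Φ(5.28 − 1.96) > 99.9%. At SD 0.5 it is higher still.
- Chi-2: the true proportions are equal, so it rejects at its 5% level at any sample size.

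**The case against.** **The regression may already be on titre.** The age- and sex-adjusted regression could use antibody level, and an article may leave that detail to a fuller plan. This stands in part: it would be wrong to say that every planned between-group analysis is binary. But the regression is a sensitivity analysis of unstated scale, introduced directly after the responder test, while the scale and test of the main comparison are fixed in the text.

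**The level is used where it matters.** The association with COVID-19 is examined on the graded scale, within each patient group. This stands. It partly meets the promise of a quantitative analysis, which is itself tied to the relation with COVID-19. It does not compare levels between the groups.

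**Responder status has a purpose.** The Discussion uses it to identify non-responders, who can be offered a booster or alternative vaccine. This stands, and it rules out demoting the responder analysis.

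**The chi-2 test is well powered at this size.** This largely stands, as the table shows. A reader might infer that the test is underpowered in general; the figures do not support that.

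Two further inferences also go too far:

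- A reader might take the Background as evidence that these three groups differ mainly in titre. The study there in which "antibody titres were significantly lower" compares patients with a control group, not kidney-patient groups with one another, and no responder rates are given. The Background also expects a lesser response in transplant recipients and cites a reduced response in solid organ transplant patients. That suggests wide responder differences in the two comparisons involving transplant recipients, where chi-2 would suffice.
- A reader might infer that antibody differences between vaccine products are hidden. The article plans no antibody comparison by product; vaccines are compared on COVID-19 incidence.

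**Conclusion.** The point holds in limited form. The only test named for the day-28 between-group comparison, and the stated outcome for the transplant analysis, use responder status although a graded value must be available. The loss is material in two situations: responder rates near the ceiling and about 1 point apart (chi-2 power about 50% to 82% in the settings run, against 97% to 100% on titres), and differences lying wholly above the cut-off, which chi-2 cannot detect at all. Both are most plausible for CKD versus dialysis.

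This rests on assumed response rates, normal log-titres with equal SD, 4000 analysed per group and pairwise testing at 5%. It is an inefficiency in a secondary endpoint. It does not invalidate the responder analysis and does not touch the primary endpoint.

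**What to change.** In the section on antibody response:

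1. Keep the responder proportions and the Pearson chi-2 test as they are.
2. Add a between-group comparison of log anti-RBD level at day 28, reported as geometric mean ratios with 95% confidence intervals and adjusted for age and sex. Name a censored (Tobit) or rank-based method for values below the assay limit.
3. State the outcome scale of the age- and sex-adjusted regression.
4. Analyse time since transplantation and immunosuppressive regimen on the log anti-RBD scale in addition to response rate.

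The cost is wording and a little more analysis, with no new samples or data. The downsides are that values below the assay limit need explicit handling and that a titre ratio is harder to communicate than a percentage, which is a further reason to report both.

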## Methods and analysis

### Study design

This is a prospective national observational cohort study which includes all kidney patients who were vaccinated against SARS-CoV-2 in the Dutch vaccination programme. Currently available vaccines in the Netherlands are the mRNA-1273 (Moderna), BNT162b2-mRNA (Pfizer), ChAdOx1 nCoV-19 (AstraZeneca) and Ad26.COV2.S (Janssen) vaccines [5–8]. Patients with CKD stages G4-G5 or on KRT received prioritization as medical high-risk group and predominantly received the mRNA-1273 vaccine in the Dutch vaccination programme. To assess the antibody dependent immune response after vaccination, blood samples will be collected at 28 days and at 6 months after the second vaccination with a home-based finger prick test. Antibody measurement will include both the receptor binding domain (RBD) of the spike (S) antigen and the nucleocapsid (N) antigen [15]. Combining these antibody measurements allows to distinguish a natural infection from an antibody response after S1-based vaccination.

Questionnaires will be obtained during a two-year follow-up period to assess the incidence of COVID-19 or (serious) adverse events ((S)AEs) after vaccination. The study events are demonstrated in Fig. 1. The questionnaires are shown in the supplemental materials.

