In our study we encountered the challenge to approach a large population to provide informed consent and obtain blood samples under high time pressure. We provided a variety of tools to overcome possible thresholds. First, the digital informed consent gave patients the opportunity to readily access study information and participation. An alternative option to apply for written informed consent was provided, thereby including patients that are not able to access digital platforms. Second by using a home-based finger prick test for antibody measurement, patients were not obliged to make travel expense to obtain blood samples and local health care workers were not burdened with more work during the pandemic. In addition, high-risk patient groups will not be exposed to an additional risk of contamination with SARS-CoV-2 due to extra visits to the hospitals. This strategy may attribute to a higher participation grade.

While our study has a real-life observational design, there are some relevant issues to mention which may impact the results. The reported efficacy depends on the presence of widespread contamination. If for any reason widespread contamination is halted, efficacy of vaccination might be confounded, hence less contamination will occur. The opposite could be the case in the midst of a pandemic where widespread contamination occurs. Additionally, participants are vaccinated according to the national Dutch vaccination programme, in which mRNA-1273 is predominantly administered to high-risk groups, including patients on dialysis or after kidney transplantation. Consequently, certain types of vaccines might be underrepresented. In this study we will only assess the humoral response following SARS-CoV-2 vaccination. Therefore, the immunogenicity of SARS-CoV-2 vaccination in high-risk kidney patients cannot be fully assessed.

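### The day-28 comparison of antibody response between CKD G4-G5, dialysis and transplant patients leaves out vaccine product, so part of any group difference could be due to product

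*Protocol article*

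**What the plan says.** All of this is in the protocol article; no separate analysis plan is shown.

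- **Main test.** Under Efficacy - Antibody response, participants are classed as responders or non-responders, proportions at day 28 are reported for each patient population, and "Pearson chi-2 test will be performed to assess whether antibody response differ between patient groups".
- **Adjustment.** The same paragraph then says: "In subsequent sensitivity analyses we will perform multiple regression analyses correcting for possible differences in age and sex between the patient groups". These two covariates are the whole list.
- **Further covariates, within one group only.** "in kidney transplant recipients we will investigate whether time after transplantation, and the different immunosuppressive regimens are associated with response rate". This does not enter the comparison between groups.
- **Products.** Study design: "Currently available vaccines in the Netherlands are the mRNA-1273 (Moderna), BNT162b2-mRNA (Pfizer), ChAdOx1 nCoV-19 (AstraZeneca) and Ad26.COV2.S (Janssen) vaccines". The next sentence says that patients with CKD G4-G5 or on KRT "predominantly received the mRNA-1273 vaccine in the Dutch vaccination programme". The Discussion returns to this: "mRNA-1273 is predominantly administered to high-risk groups, including patients on dialysis or after kidney transplantation", and warns that some products may be underrepresented.
- **Product in other analyses.** Analysis of primary endpoint compares COVID-19 incidence across the vaccines used. No such step is stated for antibody response.
- **Sampling.** Study design: "blood samples will be collected at 28 days and at 6 months after the second vaccination with a home-based finger prick test". Study enrolment aims for 4,000 patients in each of the three groups.

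**The concern.** The secondary question is whether antibody response differs between kidney patient groups. Product was assigned by the national programme, not by randomisation. If product affects the chance of being a responder and the groups differ in product mix, the crude comparison mixes the two effects. A group with more of a weaker product would look less responsive than it is, and a real deficit in a group with more of a stronger product would be partly hidden. The age and sex regression removes neither distortion.

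A large sample does not help: with 4,000 per group, random error is small but a bias from product mix stays the same size. The Discussion plans to identify non-responders as candidates for a booster or an alternative vaccine, so which groups are called poor responders has consequences.

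This is more than brevity in a condensed article. The covariates are given as a closed pair here, whereas the primary analysis gives an open list of examples and handles product explicitly.

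**Working it through.** The article gives no power, expected response rate or product share for this comparison, so there is no figure of its own to reproduce. The one arithmetic check is 3 × 4,000 = 12,000, which agrees with the abstract. What follows shows how large a product effect could be.

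**Inputs**
- n = 4,000 per group (Study enrolment).
- Responder rate 95% with mRNA and 85% with vector products, the same in every group, so kidney condition has no effect. *Assumed.*
- mRNA share m in each of two groups. *Assumed.*
- Pairwise test, two-sided 5% level. *Assumed*; the article does not say whether the test is pairwise or across all three groups.

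**Formulas**
- Pooled response in a group = 0.95m + 0.85(1 − m).
- Spurious difference = (difference in mRNA share) × 0.10.
- Chi-square = (p1 − p2)² / [p̄(1 − p̄) × 2/n], where p̄ is the mean of p1 and p2.

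**Worked case, 95% versus 80% mRNA**
- p1 = 0.95 × 0.95 + 0.05 × 0.85 = 0.945
- p2 = 0.80 × 0.95 + 0.20 × 0.85 = 0.930
- p̄ = 0.9375; variance term = 0.9375 × 0.0625 × 2/4,000 = 0.0000293
- Chi-square = 0.015² / 0.0000293 = 7.7, p about 0.006

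**Range of mixes, first group at 95% mRNA**

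| mRNA share, second group | Responses | Spurious difference | Chi-square |
|---|---|---|---|
| 90% | 94.5% v 94.0% | 0.5 points | 0.9 |
| 85% | 94.5% v 93.5% | 1.0 point | 3.5 |
| 80% | 94.5% v 93.0% | 1.5 points | 7.7 |
| 60% | 94.5% v 91.0% | 3.5 points | 36.4 |

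The last row is an upper illustration. A 35-point gap is hard to square with predominant mRNA-1273 use.

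**Chance of a significant result in the direction of the bias**, when kidney condition has no effect, from an assumed 90% response rate at 4,000 per group. The normal approximation is P(Z > 1.96 − d/SE), with SE² = [0.9 × 0.1 + (0.9 − d)(0.1 + d)]/4,000. With no bias this chance is 2.5% in each direction.

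| Share gap × product gap | Bias d | Chance |
|---|---|---|
| 2% × 10 points | 0.2 points | 5% |
| 5% × 10 points | 0.5 points | 11% |
| 10% × 10 points | 1 point | 31% |
| 10% × 20 points | 2 points | 82% |

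For d = 1 point: SE = 0.00685, d/SE = 1.46, P(Z > 0.50) = 0.31. A small difference in mix therefore does little harm; a moderate one can matter.

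**The case against.** **The groups may hardly differ in product.** Study design says that CKD G4-G5 and KRT patients alike mostly received mRNA-1273. This stands, and it limits the bias. It does not remove it, because no share is given for any group.

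**A reader might infer that the article expects unequal mixes**, since the Discussion names dialysis and transplant patients but not CKD G4-G5 when it describes mRNA-1273 use. The text does not support this. The Discussion's list is introduced as inclusive, not exhaustive, and Study design names CKD G4-G5 outright. Recruitment of CKD patients through a separate hospital cohort says nothing about which product they received.

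**A reader might also infer that time since the last dose differs between groups**, because kits are posted and samples are self-collected. That is not shown either. Sampling is set at 28 days after the second dose for all groups, and patients over 80 are excluded because they were already past that point. Spread around day 28 would confound only if it differed by group, and a sampling window may stand in the full protocol.

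**No passage compares antibody response between products, and the test uses responder status, not level.** This is fair: the product gap is an assumption, and a difference in level need not change the responder proportion. The article nevertheless treats product as worth comparing for incidence and regards an alternative vaccine as a possible remedy for non-response.

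**The expected deficit in transplant recipients may dwarf a bias of 1 to 2 points.** This may well be so. The point bites most on small contrasts, which samples of this size can declare significant.

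**Table 2 does not list product.** True, but the planned comparison of incidence across vaccines cannot be done without it.

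**Conclusion.** The point holds in a limited form. The stated between-group antibody comparison is unadjusted, with a sensitivity regression for age and sex only. Product is absent from both, although four products are in use without randomised allocation and must be known for each patient. If product shares differ between groups, part of an observed difference could be due to product; whether they differ, and in which direction, cannot be told from the article.

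Under the assumed 95% and 85% responder rates, a 15-point difference in mRNA share produces a spurious 1.5 points (chi-square about 7.7). A 5-point difference produces 0.5 points (chi-square about 0.9), which would usually pass unnoticed. It would be too strong to say that even a small difference in mix is highly significant, or that product effects will be mistaken for effects of the kidney condition. This concerns a secondary endpoint and does not touch the primary incidence analysis.

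**What to change.** - In the between-group regression for day-28 response, add vaccine product to age and sex.
- Report the same comparison restricted to mRNA-1273 recipients. This removes the product question directly, and since most patients received that vaccine it should lose little precision.
- Tabulate product by patient group, so that readers can see how much imbalance there was.
- Include actual days from the last dose to the sample only if the date is recorded and varies.

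**Cost.** A change of analysis wording. Product is already needed for the incidence comparison; the article does not document that the sampling date is recorded. Estimates for rarely used products will be imprecise, so they should serve as adjustment terms and not be read as product comparisons.

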### Outcome definitions

For an overview of the clinical endpoints in this study we refer to Table 3.

**Table 3 Tab3:** Clinical endpoints LESS-CoV-2 study

*Primary endpoint*	
Incidence (per person-year) of COVID-19 in a two-years period after SARS-CoV-2 vaccination in patients with CKD stage G4-G5 or on KRT.	
*Secondary endpoints*	
Efficacy	
• The antibody based immune response to SARS-CoV-2 vaccination at 28 days after SARS-CoV-2 vaccination.	
• The durability of the antibody response at 6 months after SARS-CoV-2 vaccination	
Safety	
• Incidence of mortality	
• Incidence of AEs of specific interest as defined by (inter) national authorities	
• Incidence of a combined endpoint of acute rejection or graft failure in kidney transplant recipients	
• Incidence of HLA antibodies defined as cPRA > 5% in dialysis patients on the waiting list for their first kidney transplantation	
*Exploratory endpoints*	
Vaccination coverage rates	
Disease severity in patients who develop COVID-19, assessed as	
• Hospitalization	
• ICU admission	
• Mechanical ventilation	
PROMs in patients on dialysis	
SARS-CoV2 genotype in patients with COVID-19 (in case available)	

*COVID-19* Coronavirus Disease 2019, *SARS-CoV-2* Severe Acute Respiratory Syndrome Coronavirus-2, *CKD* Chronic Kidney Disease, *KRT* Kidney Replacement Therapy, *AEs* Adverse Events, *HLA* Human Leukocyte Antigen, *cPRA* Calculated Panel Reactive Antibody, *ICU* Intensive Care Unit, *PROMs* Patient Reported Outcome Measures

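### Durability of the antibody response is analysed only as a change in responder status (McNemar), which does not measure how far antibody levels fall between day 28 and month 6

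*Protocol article*

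**What the plan says.** The endpoint table in the protocol article (Outcome definitions, Table 3) lists as a secondary efficacy endpoint "The durability of the antibody response at 6 months after SARS-CoV-2 vaccination", without giving a scale. The scale is set under Efficacy - Antibody response, where each participant is classed as a responder or a non-responder. For durability the section says "To assess durability of response within each patient group, we will report and compare response at day 28 with response at month 6 after vaccination", followed by "Comparison will be made using McNemar test". McNemar applies to paired binary data, so the durability comparison that the article fixes is a change of responder status within each patient group.

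The same section treats the antibody response as a quantity for another purpose. Patients with and without COVID-19 are compared on their day-28 response and again on their month-6 response: "We will examine this by use of the t-test or if more appropriate a non-parametric test". In addition, "a cut-off in the antibody response at 28 days will be defined to serve as a correlate of protection against COVID-19". Both steps need an antibody level and not only a status.

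**The concern.** Durability is naturally read as how well the day-28 response is kept. Responder status answers only part of that question, for three reasons.

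- A participant who stays above the cut-off is a concordant pair and adds nothing to the test, however much antibody has been lost.
- The test contrasts losses of response with gains. Day-28 non-responders who are positive at month 6 offset responders who have lost their response. Such gains are plausible: the Setting section describes high COVID-19 incidence, and the Antibody measurement section notes that natural infection also produces anti-RBD antibody.
- The change in responder proportion depends on the distance between a group's starting level and the cut-off. The Background expects a weaker response in transplant recipients, so the groups are expected to start at different distances.

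What is at stake is the interpretation of a secondary endpoint. A group that starts high can lose most of its antibody with little visible change, while a group that starts low can seem to wane faster at the same rate of decline.

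**Working it through.** The article gives no calculation for durability, so there is no stated figure to reproduce. The check is an illustration. Neither the cut-off nor the titre distribution is in the document, so both are assumed.

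**Model.** Log10 titre at day 28 is normal with mean m and standard deviation s. Every patient group falls by the same factor F, so the month-6 mean is m − log10(F). With cut-off c, the proportion of responders is Φ((m − c)/s) at day 28 and Φ((m − log10 F − c)/s) at month 6.

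**Assumed inputs.** c = 1.7; high-starting group m = 3.3, s = 0.5; low-starting group m = 1.9, s = 1.0.

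**Same 5-fold (80%) fall, log10(5) = 0.699:**

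| Group | Day 28 | Month 6 | Change |
|---|---|---|---|
| High start | Φ(1.6/0.5) = Φ(3.20) = 99.9% | Φ(0.901/0.5) = Φ(1.80) = 96.4% | 3.5 points |
| Low start | Φ(0.2/1.0) = Φ(0.20) = 57.9% | Φ(−0.499/1.0) = Φ(−0.50) = 30.9% | 27 points |

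A 2-fold fall (log10(2) = 0.301) in the high-starting group gives Φ(1.299/0.5) = Φ(2.60) = 99.5%, a change of 0.4 points.

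**Sensitivity.** The two groups above differ in both mean and SD, so a second illustration holds the SD equal and varies only the start. It uses log10 titres with SD 0.7, correlation 0.8 between the two times, and a 10-fold fall everywhere:

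| Day-28 median, relative to cut-off | Responders, day 28 to month 6 | Day-28 responders retained |
|---|---|---|
| 1000 times | 100.0% to 99.8% | 99.8% |
| 100 times | 99.8% to 92.3% | 92.5% |
| 10 times | 92.3% to 50.0% | 54.1% |
| 2 times | 66.6% to 15.9% | 23.7% |

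With SD from 0.5 to 0.9 and correlation from 0.6 to 0.9, retention is 98.7–100.0% at 1000 times the cut-off and 10.9–34.6% at 2 times. The geometric mean ratio month 6/day 28 is 0.10 in every row, because the fall is the same by construction.

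**What McNemar would show.** The expected statistic is n(b − g)²/(b + g), where b is the share losing response and g the share gaining it. The article intends 4000 patients per group. In the high-starting group of the first table, the net loss after a 5-fold fall is 0.035 × 4000 = 140 patients. With almost no gains the statistic is close to 140²/140 = 140, far beyond any usual threshold. At 4000 pairs the test would therefore detect this fall. What it would not show is that the loss was 5-fold.

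**The case against.** The strongest defence is that the section defines response as a status, so durability of response is whether that status holds, and McNemar is a standard test for that. If two groups decline equally and one starts near the cut-off, that group really does lose response more often. This also fits the Discussion, which wants to identify non-responders who can be offered a further vaccine. This stands: loss of responder status is a legitimate quantity, and the plan is not invalid.

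Three stronger readings are tempting, and the document does not support them.

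- A reader might infer that a large fall would be reported as durable. At the level of one patient's status, and in the retained proportion of a high-starting group, it may look so. It does not follow for the p-value, as the figure of about 140 at 4000 pairs shows.
- A reader might infer that the plan formally compares durability between groups and would find a false difference. It does not. The comparison is within each patient group, and the risk arises only when those results are read side by side.
- A reader might infer a contradiction with the key-points box, which announces "Quantitative analysis of antibody response after SARS-CoV-2 vaccination and its relationship with incidence and course of COVID-19". That sentence concerns the antibody response and its relation to COVID-19, and the analysis section does carry out that relation on a quantitative scale. It makes no promise of a quantitative durability analysis.

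The offsetting of gains and losses affects the test and not necessarily the reporting, since the paired two-by-two table separates them. An unseen analysis plan might also add titre summaries. But the comparison that the article itself fixes is binary.

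**Conclusion.** The point holds in limited form. The only durability comparison named is a within-group McNemar test of responder status. It validly tests net change in status but does not measure the fall in antibody level, although levels at both times are used elsewhere in the same section. In the illustration, one 5-fold fall appears as 3.5 points in one group and 27 points in another. The direction of this dependence on starting level follows from using a cut-off. Its size rests wholly on the assumed cut-off, means, SDs and correlation, and the real groups could lie where it is small. The primary endpoint is not affected. The change is worth making because it answers the durability question more directly at little cost.

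**What to change.** Add, as the main quantitative durability measure, the within-patient month-6/day-28 ratio of anti-RBD IgG. Analyse it as a paired difference in log titre and report it as a geometric mean ratio with 95% confidence interval for each patient group, treating values outside the assay range as censored. Beside it, report the proportion of day-28 responders who are still above the cut-off at month 6. Keep responder status with McNemar as a supplementary analysis.

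The cost is a change of wording and a small amount of extra analysis, mainly for out-of-range values. The same two finger-prick samples and the same assay serve, and no new data are needed.
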